### Statistical Considerations

#### Sample Size

The planned intake sample size is 11,000 women per arm (33,000 total). Power calculations were performed using the nQuery Advisor, version 2, software package. Rates of hr-HPV infection and associated histologically proven disease were based on results from the HART study[9], prevalence rates from the CCCaST trial conducted in Quebec and Newfoundland[8,25]. Sample sizes were based on requiring at least an 80% power to detect relative differences (alternative hypothesis) of 20% in the outcome comparisons for intervention versus control at four years and control versus safety check arms at two years.

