### Randomization and Blinding

A database has been developed specifically for the HPV FOCAL trial. Randomization occurs through this database when samples are received at the laboratory. At the time of randomization a Study Identification Number (SIN) is allocated to the participant. Samples are stratified by age and simple equal (1/3 probability) random allocation occurs at the laboratory. Upon randomization, study staff label and batch the specimens for initial processing (hr-HPV or LBC).

FPs and participants are blinded to study arm allocation. Participant results are communicated from the BCCA to the FP office as soon as they are known. If the participant's initial screening results (hr-HPV or cytology) are "negative" the report states "within normal limits". The report also states that the recommended follow-up for that participant will be communicated to the FP in two years' time. This ensures blinding is maintained for as long as possible and prevents any bias that may potentially occur from knowledge of negative results. If the screening results are hr-HPV and/or cytology positive, the results are communicated from the BCCA to the FP along with the recommended follow-up.

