### Analysis

#### Primary Outcome Measures

• Control and intervention arms: Cumulative incident ≥ CIN3 detected up to and including four years in both the control arm and the intervention arm

• Control and safety check arms: Incident ≥ CIN2 detected at two years. If the number of ≥ CIN2 in the safety-check group exceeds 0.8 times that in the control arm at the 2 year screen, then the trial will conclude and women in the four year intervention arm will be recalled at two years for their exit screen.

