#### Secondary Outcome Measures

• Rates of ≥ CIN2 and hr-HPV respectively at initial screen in control and safety/intervention arms;

• Rates of incident ≥ CIN2 at two years in control arm and at four years in intervention arm;

• The total estimated cost per woman screened and the total estimated cost per quality-adjusted life-year gained for each technology;

• Clearance of hr-HPV infection in women who are hr-HPV-positive and cytology negative at initial screen.

The primary outcome analysis will be a comparison of histologically confirmed ≥ CIN3 between the intervention and control arms. Rates of lesion occurrence will be calculated using person-time denominators for the different study intervals and compared via Kaplan-Meier plots[26]. Rates will be calculated for specific age groups within the study. Significance testing will be based on Poisson statistics and performed at the 5% level (2-sided). Analysis will also be performed using logistic regression to permit control of potential confounding factors since for some comparisons balance may not be assured by randomization. The primary comparison of disease rates between test negative groups (at entry screen) will not control for potential confounding factors since they are not balanced by randomization and the tests may select for different characteristics. Covariate-adjusted analyses will be performed to determine the extent to which any difference is explicable by potential confounders (e.g., age and sexual behaviour).

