**Contraception Method**				

Barrier (Ever)	1550 (76.8%)	1638 (77.3%)	1529 (76%)	4717 (76.7%)

Barrier (Current)	276 (13.7%)	293 (13.8%)	253 (12.6%)	822 (13.4%)

Vaginal (Ever)	197 (9.8%)	269 (12.7%)	243 (12.1%)	709 (11.5%)

Vaginal (Current)	7 (0.3%)	10 (0.5%)	11 (0.5%)	28 (0.5%)

Hormonal (Ever)	1771 (87.7%)	1829 (86.3%)	1746 (86.8%)	5346 (86.9%)

Hormonal (Current)	286 (14.2%)	291 (13.7%)	268 (13.3%)	845 (13.7%)

Permanent (Ever)	659 (32.6%)	689 (32.5%)	654 (32.5%)	2002 (32.6%)

Permanent (Current)	576 (28.5%)	626 (29.5%)	556 (27.6%)	1758 (28.6%)

Rhythm/Withdrawal (Ever)	204 (10.1%)	222 (10.5%)	176 (8.7%)	602 (9.8%)

Rhythm/withdrawal (Current)	53 (2.6%)	54 (2.5%)	39 (1.9%)	146 (2.4%)

**Duration of HRT for Menopause in Years (N = 241)**	4.2	4.5	5.6	4.7

Of the 2019 women enrolled in the control arm, 1908 (94.5%) were cytology negative. Sixteen women (0.8%) had high grade squamous intraepithelial lesions (HSIL) on their cytology evaluations, and women aged 25-29 had the highest rates of HSIL (1.4%) (Table 3). In the safety arm 92.2% of women were hr-HPV negative. The highest rate of hr-HPV positivity was in 25-29 year old women (23.5%) and the lowest rate was found in women aged 55-59 (3.7%). Similar results were obtained in the intervention arm, where 92.1% were hr-HPV negative and the highest rates of hr-HPV positivity (24.4%) were found in women aged 25-29 (Table 4).

**Table 3 T3:** Results of screening by Five Year Age Strata: Control (cytology) arm

Age Strata	Cytology Negative (%)	Cytology ASC-US (%)	Cytology ATY (%)	Cytology LSIL (mild) (%)	Cytology ASC-H (%)	Cytology HSIL (%)	Cytology Smear Unsatisfactory (%)	Total
25-29	123 (87.2)	4 (2.8)	0 (0.0)	6 (4.3)	2 (1.4)	2 (1.4)	4 (2.8)	141

30-34	157 (91.3)	1 (0.6)	1 (0.6)	9 (5.2)	0 (0.0)	2 (1.2)	2 (1.2)	172

35-39	270 (95.1)	6 (2.1)	0 (0.0)	5 (1.8)	1 (0.4)	1 (0.4)	1 (0.4)	284

40-44	302 (95.0)	3 (0.9)	1 (0.3)	6 (1.9)	0 (0.0)	3 (0.9)	3 (0.9)	318

45-49	336 (94.1)	9 (2.5)	0 (0.0)	5 (1.4)	1 (0.3)	4 (1.1)	2 (0.6)	357

50-54	296 (95.8)	4 (1.3)	0 (0.0)	2 (0.6)	2 (0.6)	2 (0.6)	2 (0.6)	309

55-59	244 (96.8)	0 (0.0)	0 (0.0)	3 (1.2)	0 (0.0)	0 (0.0)	5 (2.0)	252

60+	180 (96.8)	1 (0.5)	1 (0.5)	0 (0.0)	1 (0.5)	2 (1.1)	1 (0.5)	186

Total	1908 (94.5)	28 (1.4)	4 (0.2)	36 (1.8)	7 (0.3)	16 (0.8)	20 (1.0)	2019

ASC-US - Atypical squamous cells of undetermined significance.

ATY - Atypical Glandular Cells/NOS; Atypical Endometrial Cells/NOS; Atypical Endocervical Cells/NOS

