Data from ongoing randomized trials comparing primary screening for cervical cancer with HPV and cytology have found that HPV-based screening offers improved sensitivity for high grade CIN lesions, but with a commensurate loss in specificity. In Dillner's review[10], he noted that most cohort studies and randomized trials were limited by the number of ≥ CIN3 cases in the studies, thus reducing the statistical power to examine the screening interval using ≥ CIN3 as the endpoint. In this study, sample size calculations were conducted with ≥ CIN3 as the endpoint, resulting in the very large sample size (over 30,000 women) with the intention of having enough power to compare the incident rates of ≥ CIN3 in the control arm compared to the intervention arm. The expectation is that eventual findings of the HPV FOCAL trial will contribute to the growing body of literature examining the rapidly shifting paradigm of cervical cancer screening in the era of HPV-based technologies.

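### The stated 80% power for a 20% relative difference with 11,000 women per arm needs a control event rate above about 3.1%, which is not printed and is implausible against the trial's own entry cytology

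*Protocol article*

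**What the plan says.** The Sample Size section of the protocol article gives the size: "The planned intake sample size is 11,000 women per arm (33,000 total"). It was chosen by "requiring at least an 80% power to detect relative differences (alternative hypothesis) of 20% in the outcome comparisons for intervention versus control" (the four-year comparison), and the same requirement is applied to control versus safety check at two years. The section names the studies that supplied the rates but prints no control event rate.

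The four-year primary outcome is "Cumulative incident ≥ CIN3 detected up to and including four years in both the control arm and the intervention arm". The two-year primary outcome is incident ≥ CIN2. On testing, the Analysis section says: "Significance testing will be based on Poisson statistics and performed at the 5% level (2-sided"). Allocation is equal: "simple equal (1/3 probability) random allocation occurs at the laboratory".

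The last paragraph of the Discussion says that "sample size calculations were conducted with ≥ CIN3 as the endpoint", and presents the large size as chosen "with the intention of having enough power to compare the incident rates of ≥ CIN3 in the control arm compared to the intervention arm".

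The only outcome-related data are the entry screening results. For the control arm, Preliminary Findings reports: "Sixteen women (0.8%) had high grade squamous intraepithelial lesions (HSIL) on their cytology evaluations". The footnote to Table 3 defines HSIL to include moderate dysplasia.

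**The concern.** Sample size, significance level, effect size and power are all stated. Together they fix the one quantity left unstated, the control event rate, so that rate can be solved for and compared with the trial's own early data. It comes out at roughly three to four times the HSIL or HSIL-plus-ASC-H frequency at the control arm's entry screen.

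The article contrasts this trial with earlier studies that had too few ≥ CIN3 cases and offers its size as the remedy. If the control rate is well below 3%, a 20% difference is not reliably detectable, and a non-significant primary result would say much less about a 20% effect than the stated power suggests. The same holds for the two-year comparison, which is a primary outcome in its own right.

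**Working it through.** **Inputs.** 11,000 per arm, 80% power and a 20% relative difference (Sample Size); two-sided 5% Poisson test (Analysis); equal allocation (Randomization and Blinding). The 20% is read as a reduction relative to control, ratio 0.8. Entry cytology is from Table 3.

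**1. The plan's own figure.** 11,000 per arm cannot be reproduced forwards because the control rate is not printed. The calculation below runs backwards.

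**2. Control rate needed for ≥ CIN3 at four years.**

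- Poisson approximation: control events = (1.96 + 0.842)² × (1 + 0.8)/(1 − 0.8)² = 7.85 × 1.8/0.04 ≈ 353. As a rate, 353/11,000 = 3.2%.
- Pooled two-proportion formula, solved for n = 11,000: 3.12% (343 control events, about 618 in both arms).
- With continuity correction: 3.21%. Exact conditional Poisson test: about 3.3%.
- If the 20% is an increase over control: 3.76%.
- A one-sided test would need 2.47%, but the stated test is two-sided.

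**3. Control rate needed for ≥ CIN2 at two years, counted among entry-negative women.** Control: 94.5% of 11,000 = 10,395. Safety check: 92.2% of 11,000 = 10,142. The Poisson form gives 7.85 × (1/10,395 + 0.8/10,142)/0.04 = 3.44%. The two-proportion formula gives 3.3-3.4%.

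**4. Comparison with control-arm entry cytology (Table 3, n = 2,019).**

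| Category | Count | Percent |
|---|---|---|
| HSIL | 16 | 0.8 (95% CI 0.49-1.28) |
| HSIL + ASC-H | 23 | 1.1 (95% CI 0.76-1.70) |
| HSIL + ASC-H + LSIL + atypical glandular | 16 + 7 + 36 + 4 = 63 | 3.12 |
| Any abnormal smear (adds 28 ASC-US) | 91 | 4.5 |

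To reach 3.12% at the entry screen, all 63 women in the third row would need histological ≥ CIN3. At two years, if smears were abnormal as often as at entry, 3.3/4.5 to 3.44/4.5, or about three quarters, of all abnormal smears would have to be ≥ CIN2.

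**5. What 11,000 per arm delivers at assumed control rates** (two-proportion formula, two-sided 5%).

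| Assumed control rate | Power, ratio 0.8 | n per arm for 80% power | Ratio detectable with 80% power |
|---|---|---|---|
| 0.5% | 20% | 70,321 | 0.53 |
| 1.0% | 35% | 35,001 | 0.66 |
| 1.5% | 49% | 23,228 | 0.72 |
| 2.0% | 61% | 17,341 | 0.75 |
| 2.4% | 68-69% | about 14,400 | – |
| 3.12% | 80% | 11,000 | 0.80 |

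The exact Poisson test gives slightly lower power: 17% at 0.5%, 46% at 1.5% and 58% at 2.0%.

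**The case against.** The strongest reply is that the article prints no histological ≥ CIN3 or ≥ CIN2 rate, and that HSIL cytology at one screen is only a proxy for a four-year cumulative outcome. HSIL overstates ≥ CIN3 because it includes moderate dysplasia. It also understates it: the Colposcopy section refers ASC-H, LSIL, AGC and some ASC-US women as well, the control arm is screened three times, its exit screen adds hr-HPV testing, and the Background puts single-Pap sensitivity below 60%.

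This stands, and it limits the conclusion. A reader might infer that the trial's true power is 20-50%. The documents do not support that, because the 0.5-1.5% behind it is assumed.

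A reader might also take three times the entry HSIL rate (3 × 0.8% = 2.4%, power 68-69%) as a ceiling. It is not one. Adding ASC-H on the same basis gives 3 × 23/2019 = 3.4% and about 84% power, and three times the upper confidence limit for HSIL is 3.8%. Those scenarios need every such smear to be ≥ CIN3, with no fall in frequency after a negative screen or after treatment. They are unrealistic, but the data do not strictly exclude 80% power.

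Two further inferences should not be drawn. The absence of a stated allowance for losses is not a finding: a condensed article may leave it out, and 11,000 is described as an intake figure. Nor does the article show that prevalence was wrongly used for incidence. It names its source rates without saying how they were converted, and it does not settle whether lesions found at entry count towards the cumulative outcome.

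**Conclusion.** The power statement is not credible as written. With the stated size, test and effect, 80% power for a 20% reduction is reached only at a control rate of about 3.1-3.2% for ≥ CIN3 by four years, and about 3.3-3.4% for ≥ CIN2 at two years among entry-negative women. That threshold follows from the printed figures and holds for every two-sided variant tried with the 20% taken relative to control. Against entry HSIL of 0.8% and HSIL plus ASC-H of 1.1%, such rates are implausible.

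The size of the shortfall is conditional. At assumed control rates of 0.5-1.5%, power is about 20-49%, and the smallest reduction detectable with 80% power is about 28-47%. The documents make 80% power implausible but do not establish what the power actually is.

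**What to change.** In Sample Size, state the assumed control event rate and the population it applies to (all randomized or entry-negative women), separately for ≥ CIN3 at four years and ≥ CIN2 at two years. Check each rate against the entry results in Table 3.

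Where the rate is below about 3.1-3.4%, replace the 80% power for 20% statement with the power that 11,000 per arm gives for a ratio of 0.8, or with the ratio detectable with 80% power. Label these figures as conditional on the assumed rate. The 0.53-0.72 range above is an illustration for 0.5-1.5%, not a replacement figure to copy in. Bring the last paragraph of the Discussion into line.

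The cost is wording and one recalculation, with no added enrolment. The downside is a less favourable stated power.

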### Analysis

#### Primary Outcome Measures

• Control and intervention arms: Cumulative incident ≥ CIN3 detected up to and including four years in both the control arm and the intervention arm

• Control and safety check arms: Incident ≥ CIN2 detected at two years. If the number of ≥ CIN2 in the safety-check group exceeds 0.8 times that in the control arm at the 2 year screen, then the trial will conclude and women in the four year intervention arm will be recalled at two years for their exit screen.

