This paper describes the design and preliminary screening results of the HPV FOCAL Trial. The primary objective of the HPV FOCAL trial is to establish the efficacy of hr-HPV testing followed by liquid based cytology (LBC) triage of hr-HPV-positive women compared to LBC followed by hr-HPV triage for cervical cancer screening with ≥ CIN3 as the outcome, through a comparison of the estimated decreases in cervical intraepithelial neoplasia (CIN 2/3) that can be achieved by each screening modality in successive screening rounds. The secondary objectives of this trial are to establish the appropriate screening interval for hr-HPV negative women, using the current standard of a 2-year recall interval for cytology negative women as the benchmark of acceptable risk in British Columbia; to establish the appropriate clinical follow-up for hr-HPV positive women; and to establish the cost-effectiveness of hr-HPV testing for primary screening, all within the context of a population based Canadian cervical cancer screening program. The results of this trial will demonstrate whether or not the use of hr-HPV testing as a single primary screening test within a population based cervical cancer screening program will be able to provide further reductions in the incidence of cervical cancer and its precursor lesions, allow the screening interval to be extended, and improve the cost-effectiveness of cervical cancer screening.

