### Study Protocol (Figure 1)

In addition to the control arm and the intervention arm, a 'two year safety-check' arm is included in this trial. At the time of the trial design, there were ethical concerns identified in changing the screening interval at the same time as changing the primary screening tool in a clinical trial. To that end, we included a safety check arm, to examine the safety of hr-HPV testing within the usual screening interval. This information will be used by the data safety monitoring board to verify the safety of hr-HPV testing at the two year interval and infer the suitability of the intervention arm as the trial proceeds.

Two samples are collected during the initial screening appointment. Specimen1 (LBC) is collected first with the ThinPrep^® ^Broom-like collection device and is placed in a ThinPrep^® ^PreservCyt vial (Hologic Inc, Bedford MA) and is used for all the HPV FOCAL trial testing. Specimen 2 is collected in Digene STM^® ^(Qiagen, Mississauga ON) and is frozen for future use. Both specimens are sent to the central laboratory in Vancouver, for trial testing (specimen 1) and for storage (specimen 2). Upon sample receipt, the woman is randomized to one of the three study arms and specimen 1 is aliquoted (Figure 1). For those allocated to hr-HPV testing arms, an aliquot is removed and processed using the Qiagen sample conversion kit, and tested using the Digene Hybrid Capture 2 (HC2) assay (Qiagen, Mississauga ON), which tests simultaneously for the presence of DNA from 13 hr-HPV types. Results are classified as hr-HPV negative, hr-HPV positive or unsatisfactory. LBC testing is conducted on specimen 1 using the ThinPrep^® ^collected device, according to the manufacturer's recommendations. Cytological evaluation and reporting follow the Bethesda classification system [23].

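### The two-year rule that can end the trial compares raw ≥ CIN2 counts at a ratio of 0.8 with no allowance for chance, and so fires in about half of trials if the 20% difference used for sizing is a true reduction

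*Protocol article*

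**What the plan says.** Under Primary Outcome Measures, the second primary outcome is "Control and safety check arms: Incident ≥ CIN2 detected at two years". A stopping rule is attached to it, with this condition: "If the number of ≥ CIN2 in the safety-check group exceeds 0.8 times that in the control arm at the 2 year screen". When the condition is met, the stated consequence is that the trial ends early and the four-year arm has its exit screen at two years. No confidence limit, test, minimum number of events or denominator goes with the rule.

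Three other places in the protocol article bear on it:

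- **Sample Size.** The trial requires "at least an 80% power to detect relative differences (alternative hypothesis) of 20% in the outcome comparisons", and the comparisons covered include "control versus safety check arms at two years". The direction of the 20% difference is not stated.
- **Study Protocol (Figure 1).** The safety arm is there to let the data safety monitoring board "verify the safety of hr-HPV testing at the two year interval". The same sentence adds that the board will use the arm to judge whether the four-year arm remains suitable.
- **Background, secondary objectives.** The screening interval for hr-HPV negative women is to be set "using the current standard of a 2-year recall interval for cytology negative women as the benchmark of acceptable risk".

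Under Secondary Outcome Measures, the general analysis paragraph uses rates with person-time denominators and two-sided 5% Poisson tests. The stopping rule uses neither.

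**The concern.** A rule that acts on a bare point estimate will often act by chance when the true value lies near the trigger. Here the trigger is a ratio of 0.8, which is also a 20% reduction. If that is the difference the trial was sized to detect, the rule behaves like a coin toss in the very scenario the design is meant to handle. The article also describes the arm as a safety check at the usual interval, yet the rule fires on results that favour hr-HPV testing: with 100 control cases, 81 safety-arm cases (19% fewer) would end the trial.

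The stake is the main comparison. Once the rule fires, the four-year arm has its exit screen at two years and the planned four-year ≥ CIN3 comparison is lost.

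**Working it through.** **1. The plan's own figure.** The 11,000 women per arm can be neither reproduced nor refuted, because no base rate is given. Using the usual two-proportion normal formula with p2 = 0.8 × p1, 11,000 per arm gives 80% power (two-sided 5%) when the control proportion is about 3.1%, or about 343 control cases. One-sided, the figures are about 2.5% and 272 cases.

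**2. Model for the stopping rule.** Let C be the control count and S the safety-arm count of ≥ CIN2 at the two-year screen.

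- C ~ Poisson(m) and S ~ Poisson(m × R × k), independent.
- R is the true ratio of rates, and k is the ratio of group sizes (safety to control).
- P(stop) = P(S > 0.8 × C), summed exactly over C.

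**3. Inputs.**

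- m: assumed. If 0.5-1.1% of entry-negative control women have ≥ CIN2 at two years, then with 11,000 × 0.945 ≈ 10,400 such women, m is about 52-114, rounded to 50-115.
- k = 1 for equal groups. k = 0.922 / 0.945 = 0.976 if equal-sized arms keep the entry-negative shares in the preliminary findings (92.2% safety, 94.5% control).

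**4. Results: P(stop), %**

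| True ratio R | m = 50, k = 1 | m = 50, k = 0.976 | m = 115, k = 1 | m = 115, k = 0.976 |
|---|---|---|---|---|
| 0.5 | 2.3 | 1.8 | 0.1 | 0.1 |
| 0.6 | 10.0 | 8.4 | 2.7 | 1.9 |
| 0.7 | 26.6 | 23.2 | 17.5 | 13.6 |
| 0.8 | 49.4 | 44.8 | 49.6 | 42.7 |
| 0.9 | 71.1 | 66.8 | 80.4 | 75.0 |
| 1.0 | 86.3 | 83.4 | 95.3 | 93.1 |
| 1.25 | 99.0 | 98.6 | >99.9 | >99.9 |

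**5. Hand check (k = 1).** S − 0.8C has mean m(R − 0.8) and variance m(R + 0.64).

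- At R = 0.8 the mean is zero, so P(stop) is about one half for any m.
- At R = 1.0, z = 0.2√m / √1.64 = 0.156√m. This is 1.10 at m = 50 (86.5%) and 1.67 at m = 115 (95.3%), in agreement with the table.

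**6. Dependence on the assumed rate.** With equal groups and m from 5 to 345, P(stop) stays at 47-50% for R = 0.8 and runs from 62% to 99.8% for R = 1.0. The upper end, m = 345, is about the event count at which the 80% power in step 1 would hold. With k = 0.976, P(stop) at R = 0.8 drifts down as events accumulate, to 38% at m = 345. More events therefore do not rescue the rule at R = 0.8, and they raise the stopping probability at parity.

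**7. Effect on the four-year comparison.** A planned four-year result needs the rule not to fire. If the true two-year ratio is 0.8, the chance of reaching four years is 1 − 0.494 to 1 − 0.427 at m = 50-115, or roughly 50-57%. The overall chance of a positive four-year result cannot exceed that, whatever its power once reached.

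**The case against.** The strongest reply is that a hurdle below 1.0 may be deliberate. The board is to use the safety arm to judge the four-year arm, and crossing the line shortens that arm's interval. If hr-HPV negative women only match cytology negative women at two years, two more years unscreened might take them above the accepted risk. On that view, stopping at parity is what the rule is for. This stands as a possible intent. The article does not state it, however, and it describes the arm as a check within the usual interval.

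A reader might also infer that the rule contradicts the benchmark of acceptable risk in the Background. The article does not support this. That benchmark belongs to the objective on the screening interval for hr-HPV negative women and is not expressly the safety arm's pass mark at two years.

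Nor is the trial bound to stop. If hr-HPV testing roughly halves two-year ≥ CIN2, the rule rarely fires. The Sample Size section gives a difference to be detected, not the effect expected. If it meant a 20% increase, the trigger would not coincide with the design alternative.

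The use of counts is a smaller matter. The entry-negative totals so far (1908 control, 1954 safety) make the safety group larger, but this reflects interim arm totals of 2019 and 2119. At equal arm sizes the shares point the other way. Either effect is about 2%, though attendance at two years could add to it.

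Finally, a board charter or analysis plan, neither shown, may hold further limits. That does not remove the point: the article states a trigger and its consequence without qualification.

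**Conclusion.** The concern holds in a limited form. On either reading of its purpose, the rule acts on an observed count ratio with no allowance for sampling error and no denominator. With the 20% difference read as a reduction, it ends the trial in about 43-50% of cases when that reduction is true (50-115 control cases), in a comparison that is meant to have at least 80% power for it. With equal groups, the even chance at 0.8 does not depend on the event rate. The other figures do depend on the assumed 50-115 control cases: 83-95% at ratio 1.0, 14-27% at 0.7, 2-10% at 0.6 and about 0-2% at 0.5.

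The high stopping probability at parity is a fact about the rule. Whether it is a fault depends on an intent that the article leaves unstated.

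**What to change.** - Reconcile the secondary objectives in the Background, the purpose of the safety arm under Study Protocol, the Sample Size section and the stopping rule. State whether the two-year check tests parity with current practice or requires a reduction, and give the direction of the 20% difference.
- Express the trigger as a ratio of rates: ≥ CIN2 per entry-negative woman screened at two years, safety against control. This fits the rate-based analysis planned elsewhere in the article.
- Build in an explicit allowance for sampling error, saying which confidence limit is used and in which direction. The choice matters: with 100 control cases, stopping only when the safety rate is significantly above control (one-sided 2.5%) fires in about 2% of trials at parity and 36% at a true ratio of 1.25. A rule that continues only on a demonstrated reduction would behave very differently.
- Tabulate the stopping probabilities at true ratios such as 0.5, 0.6, 0.8, 1.0 and 1.25, and restate the four-year power allowing for the chance of stopping.

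The margin and the recall decision remain with the sponsor and the data safety monitoring board; no threshold is proposed here. The cost is rewording, a short operating-characteristics table and possibly a less favourable stated power. No extra women or tests are needed.
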